# Impact of a multimedia website with patient experiences of multiple sclerosis (PExMS) on immunotherapy decision-making: study protocol for a pilot randomised controlled trial in a mixed-methods design

**DOI:** 10.1186/s40814-020-00749-0

**Published:** 2021-01-07

**Keywords:** Multiple sclerosis, Decision-making, Decision support, Web-based experiential information, Patient experiences, Narrative information

## Abstract

**Background:**

A variety of management options (e.g. immunotherapies, lifestyle interventions, and rehabilitation) are available for people with relapsing-remitting multiple sclerosis (RRMS). Besides coping with the diagnosis, people with MS (pwMS) have to make complex decisions such as deciding about immunotherapies. In addition to factual information, reports of patient experiences (PEx) may support patients in decision-making. The added value of PEx in decision-making is not clear, and controlled studies are rare. Therefore, systematic methods are necessary to develop and analyse PEx. As there are no evaluated PEx for MS in Germany, we are currently creating a website presenting PEx structured according to topics and illustrated by video, audio, and text files. We aim to determine the feasibility of an intervention using PEx and evaluate whether PEx may help pwMS in their immunotherapy decision-making processes as a supplement to evidence-based information.

**Methods:**

This project will follow the Medical Research Council framework for development and evaluation of complex interventions. After the development of a website with PEx, a randomised controlled pilot trial (pilot RCT) will be conducted in 2–3 MS centres, clinics, or rehabilitation centres including 55 pwMS and accompanied by a process evaluation. Patients with a RRMS diagnosis considering immunotherapy are eligible. The primary outcome is decision self-efficacy. Secondary outcomes include preparation for decision-making, decisional conflict, risk knowledge, confidence in active participation, affective forecasting, social support, and self-reported impact of eHealth on its users. Participants will be randomly assigned either to (i) an intervention group with 4 weeks access to an evidence-based patient information resource and the PExMS-website as an adjunct or to (ii) the control group with access to evidence-based information alone. A 6-member advisory panel involving representatives of pwMS, researchers, and neurologists, who accompany the whole project, will mentor this pilot RCT.

**Discussion:**

The intervention was developed with systematic methods, created with active patient involvement and in critical appraisal by an expert advisory panel. The study is innovative as it contributes to the controversial evidence on the use of PEx in the context of evidence-based patient information.

**Trial registration:**

ClinicalTrials.gov, NCT04236544

**Supplementary Information:**

The online version contains supplementary material available at 10.1186/s40814-020-00749-0.

## Background

Multiple sclerosis (MS) is a chronic, degenerative disease of the central nervous system, which is causing remitting and progressive physical and psychological dysfunctions. Three major disease course forms of MS can be separated: relapsing-remitting MS (RRMS) (the most frequent type), secondary progressive MS (SPMS), and primary progressive MS (PPMS). Many people with MS (pwMS) are diagnosed at age 20 to 40, mostly with RRMS [1, 2]. In Germany, about 200,000 cases are prevalent [3].

For RRMS, 18 disease-modifying therapies are available, but those are only partially effective. Most of them have substantial side effects, in the worst-case life-threatening. The long-term effectiveness remains unclear. Moreover, other approaches such as lifestyle interventions, rehabilitation, and so-called complementary alternative therapies might be helpful [4, 5]. This makes the decision-making process for such treatments complex, while at the same time, the information needs of pwMS are often not met [6–8].

Information provision with carefully developed decision aids including group education [9] and face-to-face coaching [10] bears positive outcomes and is urgently needed but not everywhere available. Among chronically ill people, pwMS are among the most frequent internet users being confronted by an overwhelming amount of web-based information of variable quality and aims [11–13].

When faced with new health concerns or treatments, patients search not only for fact-based information but also seek other patient experiences (PEx) [14]. There is limited but increasing research looking at the value of PEx [14–24]. The design and quality of these studies including PEx as an intervention varies [18, 24]. Also, there is no agreed-upon operationalisation of PEx, which are also called narratives, exemplars, anecdotes, testimonials, or case histories [24]. This study will use the term PEx, specifically to denote online messages of patients in first-person as text, audio, or video files.

Little is known on the outcomes of PEx, especially how they influence decision-making [18, 24]. PEx have the potential to enhance the motivation in engaging with patient decision aids and the perceived experience of using it, especially in a population with lower health literacy [18]. According to cognitive learning theories, experiential information allows people to process, store, and save information more effectively than didactic information because it is vivid [17, 23, 25]. Moreover, patients have trouble forecasting feelings, especially their intensity and duration, which results in inaccurate affective forecasts [26]. PEx may increase the perceived ability to make accurate affective forecasts, which is the peoples’ prediction about how they will feel during future or imagined events. People used to focus on losses rather than continuity or even potential gain. Also, they fail to envision how their coping skills will help to manage the new situation and develop adaptation, which is important in decision-making processes [27]. Through PEx, patients may gain feelings of control and confidence facilitating self-management and coping uncertainty [16, 17, 23, 25, 28].

The internet provides a wide range of opportunities to share and learn about other PEx via blogs and discussion groups. Different motivations and mostly negative or dramatic experiences within the health system drive contributors to social media platforms, which lead to a selective picture of the disease, treatments, and health care resources. More numerous but inconspicuous PEx remain unnoticed. Beyond the huge amount of free-floating information on the web, concerns exist about the use of experiential information because of considerable risks of selectivity and biased information even if presented along with balanced information [25]. Looking at poor existing evidence of PEx, while not differentiating between varying kinds, the German ‘Guideline Evidence-based Health Information’ does not recommend narratives being part of evidence-based health information [29].

However, the high usage of social media strongly underlines pwMS’ needs of PEx. Therefore, there is an unmet need for care-oriented research on making PEx accessible and studying their impact. To our knowledge, there are no evaluated PEx in MS in Germany so far. This pilot randomised controlled trial (pilot RCT) will be the first testing of an intervention including PEx of MS (PExMS) as video and audio files, gained through a systematic qualitative research approach.

## Objectives

By embedding a process evaluation within the pilot trial, the primary study objective is to test the feasibility of an intervention using PEx as a supplement to evidence-based information to establish whether it is possible to carry out a large future RCT. The specific objectives are to determine the following:
Acceptability of recruitment, randomisation, and consent procedureAcceptability and feasibility of collecting reliable and valid data on primary and secondary outcomesAcceptability of the intervention and processes to participants and clinical staffSuitability of the intervention usedBarriers to adherenceExplore aspects of the trial design and conduct with a patient and public involvement group

We hypothesise that PEx may help pwMS in the decision-making process for or against immunotherapy or their different forms, respectively. Therefore, the secondary objectives are (1) to obtain pilot data on the likely difference between the intervention and evidence-based information alone regarding decision self-efficacy; (2) to inform the sample size calculation for the substantive randomised clinical trial; and (3) to control for potential bias caused by PExMS.

## Methods

### Trial design

The PExMS project follows the guidance of the Medical Research Council [30] for the development and evaluation of complex interventions and adheres to the SPIRIT checklist (see Additional file 1). The process has a development as well as a feasibility and piloting phase.
Development: The PExMS website was developed within a qualitative interview study, where PEx were collected (see ‘Intervention description’).Feasibility and piloting: First, people with RRMS (see ‘Intervention description’) will be asked about their experiences with the PExMS website (e.g. usability, acceptance, layout, navigation) and the outcome measurement procedures.Second, in a two-arm pilot RCT, we will compare a combination of the PExMS website and evidence-based patient information with evidence-based patient information alone. The pilot trial is intended to test recruitment, outcome measures, data collection (sampling and timing), randomisation procedures, and acceptability of the intervention for pwMS and practitioners, and gain exploratory results that could be used for sample size estimations in future RCTs. We want to assess whether the intervention was conducted as intended (fidelity) and assess the quantity of the implemented intervention (dose).A mixed-methods process evaluation will be applied. In the recruitment phase, we will perform semi-structured telephone interviews with all responsible persons in participating centres to assess perceptions of strengths, weaknesses, risks, and opportunities of the study.After completing the study, centres which succeeded in recruitment and centres that dropped out prematurely or failed in recruitment will be interviewed and will be asked to fill out a process evaluation questionnaire to assess acceptability of the recruitment, randomisation and consent procedure, and the intervention itself.Additionally, approximately 10 patients, namely maximum users and minimum users, of the PExMS-website and those having dropped out will be interviewed in each group and will be requested to complete a process evaluation questionnaire.

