### Strategies to improve adherence to interventions

All participating neurological practices, clinics, or rehabilitation centres will receive a study folder including all relevant documents. Also, regular phone calls and telephone conferences will be conducted for arising questions and updates and for sharing experiences.

Usage of the intervention will be monitored by tracking the site visits. PwMS will be contacted by regular email reminders by a member of the coordinating centre to use the intervention. In case of non-use, participants will be reminded by email or telephone.

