### Outcomes

#### Primary outcomes

Primary outcomes will be assessed by mixed-methods consisting of interviews and process evaluation questionnaires, which include the following overall feasibility and process-related measures:
Number of participants consented, recruited, randomised, withdrawn, and retainedNumbers with completed outcome measures or lost to follow-upAcceptability of the intervention in terms of frequency and duration of usage as well as experience, motivation, barriers, and facilitators to use the intervention—from the pwMS and participating study centre perspectiveAcceptability of the study procedures in terms of barriers and facilitators to implementation—from the pwMS and participating study centre. We will also ascertain the number and type of adaptations made to implementation strategies including information on how and why.

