We will assess patients’ preferences for involvement in treatment decisions by the 5-item Control Preferences Scale (CPS) [44]. In a validation study, a Cronbach’s alpha of 0.72 was attained [45].

PEx may give pwMS confidence in active participation and management in medical care [46]. Therefore, the 13-item ‘Patient Activation Measure 13’ (PAM13-D) [47] will be used which is a reliable and valid measure of patient activation with a four-point-Likert scale. It shows good internal consistency achieving a Cronbach’s alpha of 0.87 [47].

The eHealth Impact Questionnaire ‘eHIQ’ [46, 48] measures attitudes of users towards a website which they recently viewed. It is divided into the 11-item eHIQ-Part 1 and the 26-item eHIQ-Part 2. The former represents general attitudes towards using the internet to access health information. The second part is related to the effects of using a specific health-related website on three subscales: (1) confidence and identification, (2) information and presentation, and (3) understanding and motivation. Both answering formats range from 1 ‘strongly disagree’ to 5 ‘strongly agree’. The eHIQ shows good internal consistency achieving a Cronbach’s alpha of ≥ 0.77. A German translation will be validated and used. Moreover, identifying with others who show their experiences on a website, knowing that other pwMS are handling similar problems and learning how they manage difficult issues can reduce the feeling of isolation and improve the sense of social support and group membership [14, 25]. Reformulated items from the subscale ‘confidence and identification’ of the eHIQ will be used to assess social support.

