### Confidentiality

All data collected during the study will be kept strictly confidential. All electronic data from the pilot RCT will be pseudonymised and there will be no possibility to link data to persons without access to the code list. Through the personal access of patients to the PExMS website or DECIMS-Wiki based on a personal account (sent via email), it will be possible to individually track the use of the websites (e.g. frequency, use of different parts), which will be used to analyse user behaviour and the feasibility of the study design. User’s IP address will be stored by the system but shielded to anyone but the system administration. A personal account name will be used to connect users and pseudonyms.

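### The patient-reported part of the primary acceptability outcome rests on a questionnaire assigned only to a purposive subset that omits typical users and nearly all controls

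*Protocol article*

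**What the plan says.** Under Primary outcomes the protocol article states: "Primary outcomes will be assessed by mixed-methods consisting of interviews and process evaluation questionnaires". The list that follows has trial-wide counts (consent, randomisation, withdrawal, retention, completed measures) and two acceptability items. Acceptability of the intervention covers frequency and duration of use, and also experience, motivation, barriers and facilitators. Acceptability of the study procedures covers barriers and facilitators to implementation. Both are to be obtained from patients and from centres.

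Trial design says who is asked. Centres are interviewed and "will be asked to fill out a process evaluation questionnaire to assess acceptability of the recruitment, randomisation and consent procedure, and the intervention itself". On the patient side it names "approximately 10 patients, namely maximum users and minimum users, of the PExMS-website" and continues: "those having dropped out will be interviewed in each group and will be requested to complete a process evaluation questionnaire". No other sentence assigns the questionnaire to patients, and Table 1 does not list it at any time point.

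Other sources do cover participants generally. Under Strategies to improve adherence: "Usage of the intervention will be monitored by tracking the site visits". Under Confidentiality, through personal accounts on either website, "it will be possible to individually track the use of the websites". The eHIQ, a secondary outcome, "measures attitudes of users towards a website which they recently viewed"; its Part 2 is scheduled at t1 with no restriction to a subset.

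**The concern.** Picking the heaviest users, the lightest users and the drop-outs is a sound way to choose interviewees, because it widens the range of views heard. It is a poor way to choose respondents for a questionnaire that serves a primary outcome. The respondents are selected on usage or drop-out, usage is itself one component of that outcome, and the patients in the middle are excluded by design. Neither the complete-case analysis nor the imputation described under Analysis can recover answers from people who were never asked.

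The rule also fits the control arm badly. Only the intervention group has access to the PExMS website, so a control patient cannot be a maximum or minimum user of it. Yet the acceptability of consent, randomisation and data collection concerns controls just as much.

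At stake is the first stated purpose of the pilot. A decision on a large trial would draw on patient-reported acceptability that describes the extremes of one arm and some drop-outs.

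**Working it through.** The protocol gives no precision target for acceptability, so there is no figure of its own to reproduce. The check has four steps.

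**Inputs from the document.** Total sample 55 (Sample size); 1:1 allocation (Sequence generation), so 27 or 28 per arm; about 10 patients selected (Trial design); drop-out target below 20% (Analysis). **Assumptions, not in the document:** true acceptability of 70%, and 80% as an alternative.

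**1. How many are asked.** The word group is not defined, so there are three readings:

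| Reading | Asked | Share of 55 | Not asked |
|---|---|---|---|
| 10 in total | 10 | 18% | 45 |
| 10 per trial arm | 20 | 36% | 35 |
| 10 in each of three categories (maximum, minimum, drop-out) | 30 | 55% | 25 |

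**2. Whether controls can be reached.** Controls can qualify only as drop-outs, whichever reading is taken. The drop-out target allows fewer than 0.20 × 55 = 11 in the whole trial, so at most 10. Spread evenly over the arms, that is about 5 controls. If the trial meets its own target, ten control respondents would be available only if every drop-out came from the control arm. Step 3 nevertheless uses 20 for the pooled figure, which is generous to the plan.

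**3. Precision if the respondents were a random sample.** Half-width = 1.96 × √(p(1 − p)/n), with p = 0.70:

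- One arm, n = 10: 1.96 × √(0.21/10) = 0.284, about ±28 points.
- One arm, n = 27: 1.96 × √(0.21/27) = 0.173, about ±17 points.
- Both arms, n = 20: 1.96 × √(0.21/20) = 0.201, about ±20 points.
- Both arms, n = 55: 1.96 × √(0.21/55) = 0.121, about ±12 points.
- Both arms, n = 44 (0.80 × 55, those left at 20% drop-out): 1.96 × √(0.21/44) = 0.135, about ±14 points.

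The normal approximation is rough at n = 10. Wilson 95% intervals at an assumed 80% give the same picture: 49% to 94% with 10, 62% to 91% with 27, 66% to 89% with 44 and 68% to 88% with 55.

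**4. What selection adds.** Suppose 8 of 10 selected patients in an arm of 27 find the intervention acceptable. The 17 not asked could all say no or all say yes, so the arm value could lie anywhere from 8/27 = 30% to (8 + 17)/27 = 93%. Because the ten are not a random draw, a confidence interval based on them does not narrow this range.

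**The case against.** The strongest reply is that the plan sets no quantitative acceptability estimand. The process evaluation is mixed-methods, interviews are analysed thematically, and the only numeric feasibility targets (drop-out below 20%, questionnaire response above 60%) are defined on all participants. For exploratory content such as barriers and motivation, extreme-case sampling is legitimate. This stands for the interviews. It does not settle the matter for the questionnaire, which is named as an instrument for a primary outcome and would reach more patients at little cost.

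Three stronger readings are tempting and are not supported:

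- *A reader might infer that acceptability is not estimated for the trial population at all.* Use is tracked individually in both arms with consent, retention and completion are counted for everyone, and eHIQ-Part 2 goes to all at t1. Centres also receive a process evaluation questionnaire. But tracking shows what was used and not why, and the eHIQ as described concerns a website, not consent, randomisation or trial procedures.
- *A reader might infer that the rule yields nothing for controls.* Control drop-outs are covered, and centre interviews, control-arm counts and DECIMS-Wiki tracking add information.
- *A reader might set ±28 points (n = 10) against ±12 (n = 55).* That is not like for like. PExMS acceptability can be asked only in the intervention arm, so 10 must be compared with 27, and the pooled 20 with 55.

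It can also be said that the text does not forbid giving the form to others, and that a condensed article may leave its distribution to the full protocol. That is possible. But the article does fix a patient rule, and what it fixes is the extreme-case subset.

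**Conclusion.** The concern holds in a limited form. As written, patients' experience, motivation, barriers, facilitators and views of study procedures come only from a small subset chosen on usage or drop-out, with typical users left out and controls present only as drop-outs. These components cannot be summarised as a proportion or mean for the trial population. The loss of precision is moderate on a like-for-like basis: about ±28 against ±17 points within an arm, and about ±20 against ±12 pooled. The selection problem is the more serious part, because its direction and size depend on patients who are never asked.

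The half-widths rest on an assumed 70% acceptability, on full response, and on reading the rule as ten per arm. The omission of typical users and of continuing controls does not depend on these assumptions. The change is worth making because it is cheap, bears on the primary objective, and can still be made: the article states that recruitment has not begun.

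**What to change.** - Send the process evaluation questionnaire to all randomised participants in both arms as the last form of the t1 web battery, and offer it to drop-outs when they withdraw.
- Keep the maximum-user, minimum-user and drop-out sampling for the interviews only.
- Define the word group in that sentence, and say whether drop-outs are included in the ten or additional to it.
- Select control interviewees by their DECIMS-Wiki use, which is already tracked.
- Add the questionnaire to Table 1.

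The cost is one more form in an online survey that already exists. The downside is a longer t1 session: Table 1 already schedules 11 instruments there, including the 26-item eHIQ-Part 2. Placing the form last limits any effect on completion of the other outcomes.

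If the sponsor prefers not to extend the battery, the minimum is to state that the patient questionnaire findings describe a purposive subset and not the trial population, and that trial-wide acceptability rests on tracked use, retention, completion and eHIQ-Part 2.

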### Study setting

The study will be conducted in different participating neurological practices, clinics, or rehabilitation centres located in Germany.

